| Follow-up duration | 
Daily visits for tolerability:
Day: 1, 2 and 7 are at clinic and the remainder at home
 
Safety and immunogenicity key visits:
Day 14, Day 28, Day 56, Day 84, and Day 180 post vaccination
                                                                                                                                                                                                                                                                                                                                                                                                                                                                                                                                                                                                                                                                                                                                                                                                                                                                                                                                                                                                                        |
| Planned Trial      | 
November 2014 to December 2015 for recruitment and interim follow
                                                                                                                                                                                                                                                                                                                                                                                                                                                                                                                                                                                                                                                                                                                                                                                                                                                                                                                                                                                                                                                                                                                                                                             |

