### 4.3. Endpoints

#### Primary Endpoints

The nature, frequency, and severity of adverse events (AEs) and/or serious adverse events (SAEs) associated with administration of BPSC1001 at 5 different doses measured as follow:

- Frequency and severity of local injection site reactogenicity signs and symptoms: pain, erythema, and induration until day 14 post vaccination (solicited local symptoms)
- Frequency and severity of systemic reactogenicity signs and symptoms until day 14 post vaccination (solicited general symptoms)
- Frequency of adverse events (AEs), severity and assessed relationship to study products until day 28 post vaccination (unsolicited AE)
- Detailed description of all serious adverse events (SAEs) until day 28 post vaccination
- Distribution of values of safety laboratory measures at baseline and at follow-up visits post-vaccination until day 28 post vaccination (reference ranges will be age appropriate)
- Number of participants with early discontinuation of vaccinations and reason for discontinuation until day 28 post vaccination

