### **6.3. Study Enrollment/ vaccination (Visit 2, Day 0)**

Vaccination with BPSC1001 will occur at Visit 2. Potential participants will be listed upon information sessions and their willingness to participate. They will be then screened by block of 5-10 volunteers after informed consent signature. Eligible participants will be given a study identification number which for adults will be used for random selection to one of 5 cohorts. The randomization will be done using a software. The randomization will be detailed in a study procedure.

Subjects will have only one vaccination visit during the course of the study. Each subject will receive an injection of BPSC1001 into the outer aspect of the subject's upper arm (deltoid area). The following procedures will be performed during each injection visit:

- Review of subject's medical history (including concomitant medications) since previous visit

- Check of inclusion / exclusion criteria
- Directed physical examination (proposed injection site) and vital signs check
- Urine sample collection for determination of:  
Urine pregnancy test (females only)\*
- Injection with study product
- Post-injection observation period of at least 60 min.
- Study visits schedule , thermometer ( for axillary temperature), and ruler distribution and review of use
- Provision of emergency contact card
- Repeat examination of injection site and vital signs check
- Review of any immediate AE

\*All female subjects of childbearing potential will be required to submit a urine sample for onsite pregnancy testing on the day of injection, and the test results must be negative prior to administration of the vaccine.

#### 6.4. Follow-Up Visits: visit 3 to visit 10

There will be 8 follow-up visits (Visits 3 through 10). Table 3 outlines visits, study days, and visit windows. The following procedures will be performed during each follow-up visit:

- Review of subject's medical history (including concomitant medications and AE) since previous visit
- Directed physical examination and vital signs check
- Review solicited symptoms (4 visits; Visits 3, 4, 5, 6, )
- Collection of approximately 6 to 92 mL whole venous blood for the determination of:
  - WBC
  - Serum chemistry profiles (Creatinin, AST, ALT) will be performed only at visits 5,7,9,10.
  - Blood for immunological analyses
  - Blood for virus isolation
- Urine and saliva for virus isolation

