## **Solicited Adverse Events**

A solicited AE is a predetermined event, which may reflect safety concerns related to the investigational product. The solicited AEs for this study include:

- Swelling, or pain at site of injection
- Fever
- Chills
- Myalgia (described to the subject as generalized muscle aches)
- Arthralgia (described to the subject as generalized joint aches)
- Swelling of joint(s) or pain on motion of joint(s)
- Rash or blisters of the skin
- Blisters or ulcers in mouth, tongue or gums
- Fatigue
- Headache
- Gastrointestinal symptoms (nausea, vomiting, abdominal pain, and/or diarrhea)

Participants with objective signs of arthritis (swelling, tenderness, warmth etc) will be evaluated with ultrasound.

Vesicular lesions and joint effusions (if tapped) will be sampled for PCR and virus isolation.

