### Recording Adverse Events

### Methods/Timing for Assessing, Recording, and Analyzing Safety Endpoints

Solicited AEs will be reviewed within the 14 days of vaccination utilizing the provided study memory aids. When a diagnosis is known, the AE term recorded on the CRF will be the diagnosis rather than a constellation of symptoms. The investigator will assess all AEs for seriousness, relationship to investigational product, severity, and other possible etiologies. When an event has not resolved by study closure, it will be documented on the AE CRF as “ongoing”.

The timeframe for the collection of unsolicited AEs begins at the first administration of investigational product through 28 days after the investigational product is administered. Solicited AEs will be collected from the time of administration of investigational product through 14 days following the procedure (assisted with a memory aid). The timeframe for the collection of SAEs begins at the first administration of investigational product through the end of the study.

All adverse events will be reported in concordance with ICH GCP reporting guidelines, with expedited reporting of SAEs being determined by these guidelines as well.

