#### Exploratory Endpoints:

There are multiple exploratory endpoints related to the immunological response to the vaccine. Endpoints include:

- Cross-neutralizing antibodies GMT using other Ebola PsV (eg, Sudan)
- Epitope studies with Ebola glycoprotein as target
- Human subjects will be genotyped based on HLA allele expression.
- Evaluation of the B cell repertoire before and after vaccination via Ig VDJ rearrangement sequencing and Ig heavy chain characterization
- Serum immunoglobulin characterization via mass spectrometry/proteomic analysis
- Characterization of epitope targeting for humoral response via domain programmable arrays
- Analysis of T cell repertoire via T cell receptor characterization
- Using multicolor flow cytometry, characterization of cellular response to vaccine antigen or peptides by intracellular cytokine staining (ICS) and the presence of surface markers that indicate cell lineage (CD4+, CD8+), activation status, and expression of selected activation markers.

- Isolation of Human Antibodies

The vaccine is eliciting a broad range of neutralizing antibodies. The genetic information of these antibodies can be isolated by the technology of phage display. For this, whole blood needs to be preserved in one Serum tube (2.5ml whole blood) and four PAXgene Blood RNA tubes (each tube à 2.5 ml whole blood). This blood withdrawal is needed 4 weeks after the last boost. From this blood whole RNA will be isolated, cDNA generated and the gene information from the variable fragments of the antibodies cloned into an appropriate phagemid system. From the resulting Fab-Phage Display Library, specific antibody fragments will be isolated, recombinantly produced and characterized for specific binding. The parallel blood withdrawal of serum is needed for preliminary tests of the blood samples for specific antigen reactivity.

|                                                          | Visit 1
Screening
Day -30/-1 | Visit 2
Vaccination
D0 | Visit 3
Follow-up
D1 | Visit 4
Follow-up
D2 | Visit 5
Follow-up
D7 | Visit 6
Follow-up
D14 | Visit 7
Follow-up
D28+/-7 | Visit 8
Follow-up
D56+/-7 | Visit 9
Follow-up
D84+/-7 | Visit 10
Follow-up
D180+/-14 |   |

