### **Adverse events**

An AE is any untoward medical occurrence in a subject that may occur during or after administration of an Investigational Medicinal Product (IMP) and does not necessarily have a causal relationship with the intervention. An AE can therefore be any unfavorable and unintended sign (including an abnormal laboratory finding), symptom or disease temporally associated with the study intervention, whether or not considered related to the study intervention.

Each AE will be graded according to the tables for AE severity below. The following guidelines will be used to determine whether or not an AE is recorded in the study database:

- Solicited AE (*i.e.*, reactogenicity parameters) will be recorded on diary cards in the seven days and recorded in the CRF in the 14 days following injection
- Unsolicited AE of all severities will be recorded on diary cards in the seven days and recorded in the CRF in the 28 days following injection
- After Day 28 and throughout the remainder of the study period, only SAE will be recorded in the CRF

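### The collection rules for the primary safety endpoint contradict each other on diary length, erythema and the Day 28 cut-off, and may under-ascertain events

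*Protocol*

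**What the plan says.** **Endpoint windows.** Section 4.3 (Primary Endpoints) counts local reactions, "pain, erythema, and induration until day 14 post vaccination (solicited local symptoms"), systemic reactogenicity to Day 14, and unsolicited AEs to Day 28.

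**Solicited AEs, main text.** Section 6.5 (Recording Adverse Events) states: "Solicited AEs will be reviewed within the 14 days of vaccination utilizing the provided study memory aids". The synopsis endpoints and the safety endpoint specification in 6.5 also give 14 days with a memory aid. Section 6.4 schedules the review at four visits: "Review solicited symptoms (4 visits; Visits 3, 4, 5, 6". These fall on Days 1, 2, 7 and 14.

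**Solicited AEs, safety annex (Adverse events).** They "will be recorded on diary cards in the seven days and recorded in the CRF in the 14 days following injection".

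**Solicited AEs, synopsis (Follow-up duration).** Tolerability visits are daily: "Day: 1, 2 and 7 are at clinic and the remainder at home". No end day is given.

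**Solicited list.** The only injection-site entry in Section 6.5 (Solicited Adverse Events) is "Swelling, or pain at site of injection". The annex scale for local reactions grades redness/erythema in millimetres and asks for the measurement as a continuous variable too.

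**Unsolicited AEs.** The Table 3 header reads "Visit 7 Follow-up D28+/-7". The Monitor AEs row is marked at Visits 2 to 7 and blank at Visits 8 to 10. Section 6.4 asks for an AE review since the previous visit at every follow-up visit. The annex's reporting procedures require all AEs occurring within 28 days of injection to go into the CRF. The annex also says: "After Day 28 and throughout the remainder of the study period, only SAE will be recorded in the CRF".

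**The concern.** AE frequency is the primary endpoint, and Section 7 compares the percentage of participants reporting AEs between groups with Fisher's exact test. That comparison is only as good as the uniformity of collection. Staff working from the annex would run a seven-day diary. Staff working from Section 6.5 would run a 14-day memory aid. Staff working from the solicited list would not ask about redness at all. An AE starting on Day 24 in someone seen on Day 21 could be recorded or refused, depending on which passage is followed.

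Cohorts are enrolled partly in sequence. If practice changed between them, differences in ascertainment could be mistaken for differences between doses or age groups. The issue was still live when Amendment 3 was submitted: Section 4.1 reports 60 participants vaccinated, which left 201 - 60 = 141 to come.

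A statistical analysis plan cannot repair this, because it cannot analyse data that were never collected.

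**Working it through.** The protocol states no figure to reproduce here. The check compares passages and does window arithmetic.

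**1. Diary length**
- Inputs: endpoint to Day 14 (4.3); diary for seven days (annex); solicited review on Days 1, 2, 7 and 14 (6.4, Table 3).
- With the seven-day diary, the days with neither a diary entry nor a visit are Days 8 to 13: 13 - 7 = 6 days, and 6/14 = 43%. Day 14 is itself a visit.
- With the 14-day memory aid of Section 6.5, the gap is 0 days.
- The synopsis home visits could also close the gap, but neither 6.4 nor Table 3 contains them.
- Section 6.3 lists a visit schedule, thermometer, ruler and emergency card as handed out at Day 0. It lists neither diary nor memory aid.

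**2. Erythema**

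| Source | Pain | Induration/swelling | Erythema |
|---|---|---|---|
| Primary endpoint (4.3) | yes | yes | yes |
| Annex grading scale | yes | yes | yes |
| Solicited list (6.5) | yes | yes | no |

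One of the three named local symptoms has an endpoint and a scale but is not solicited.

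**3. Day 28 window**
- Visit 7: 28 - 7 = Day 21 to 28 + 7 = Day 35. Visit 8: 56 - 7 = Day 49 to 56 + 7 = Day 63.
- Largest stretch after the last marked AE visit: 28 - 21 = 7 days, and 7/28 = 25%.
- If Visit 7 were spread evenly over Days 21 to 35 (an assumption), the mean stretch would be (7+6+5+4+3+2+1)/15 = 28/15 = 1.87 days, and 1.87/28 = 6.7%.
- This stretch is lost only if Visit 8 is not used. An AE with onset on Day 24, first mentioned at Visit 8, is treated as follows:

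| Passage | Treatment |
|---|---|
| Section 6.4 | asked about |
| Annex, reporting procedures | recorded, because it occurred within 28 days |
| Table 3, Monitor AEs row | no AE monitoring at Visit 8 |
| Annex, SAE-only line after Day 28 | unclear: the cut-off could mean onset or date of reporting |

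**4. How many events could start in each stretch**

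The protocol gives no onset times, so this is an assumption shown over a range. If onset decays with half-life h days, the share of events in a window of T days that start between days a and b is (2^(-a/h) - 2^(-b/h)) / (1 - 2^(-T/h)).

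| h | Days 8-13 of 14 (a=7, b=13) | Days 22-28 of 28 (a=21, b=28), Visit 7 on Day 21 |
|---|---|---|
| 3 days | 15% | 0.6% |
| 7 days | 30% | 6.7% |
| 14 days | 36% | 13.8% |
| flat | 43% | 25% |

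These are shares exposed to weaker collection, so they are upper limits on loss. Recall at the Day 14 visit or at Visit 8 would recover some of them.

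**The case against.** The strongest reply is that the recording windows match the endpoint windows. The annex sentence that limits the diary to seven days continues CRF recording to Day 14, and the next item continues it to Day 28. Section 6.4 reviews solicited symptoms on Day 14 and AEs at every follow-up visit. The annex's reporting rule depends on when an event occurs, so the SAE-only line reads naturally as an onset cut-off. Erythema has a grading scale, and rulers are issued.

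Most of this stands. A reader might infer that AE recording stops before the primary windows close, or that the frequencies are undercounted. The documents support neither: recording runs to Days 14 and 28, and no AE rates, onset times or recall errors are given from which a deficit could be shown.

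A reader might also infer that non-serious joint events starting after Day 28 bias the primary endpoint, since Section 4.6 mentions arthritis cases in another trial of the vaccine. They cannot, because the primary window ends at Day 28. The limit for non-serious events is applied consistently as a design choice, and Section 4.6 gives no onset times to argue against it.

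The reply does not remove the conflict over diary length, the omission of erythema from the list that tells staff what to ask, or the blank Visit 8 cell beside an ambiguous cut-off.

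**Conclusion.** The concern holds as an internal inconsistency that may lead to under-ascertainment of the primary safety endpoint. It should be fixed.

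- **Diary:** six of 14 solicited days (43%) rest on recall if the annex governs, and none if Section 6.5 governs.
- **Erythema:** one of three named local symptoms would have no systematically solicited frequency if the list in 6.5 is followed. It could still be found on examination or reported spontaneously.
- **Day 28 window:** at most seven of 28 days (25%) are in doubt, for a participant seen on Day 21. The mean is 6.7% if visit timing is uniform. The doubt disappears if the cut-off means onset and Visit 8 is used.

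The size of any actual loss cannot be estimated from the protocol. The reading of Table 3 assumes that the marks in the Monitor AEs row line up with Visits 2 to 7, as they do in the extracted table.

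**What to change.** 1. In the safety annex and Section 6.3, specify one diary or memory aid, issued at Day 0 and covering Days 0 to 14. Use one name for it throughout.
2. Add injection-site erythema to the solicited list in Section 6.5.
3. State in the annex that the Day 28 cut-off refers to AE onset. Mark Visit 8 in the Monitor AEs row of Table 3, so that AEs with onset up to Day 28 that Visit 7 did not capture are recorded there.
4. Reconcile the daily home visits in the synopsis with Section 6.4 and Table 3, and give their end day if they are kept.

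The cost is slightly more diary and CRF entry. The first three changes use visits already scheduled and rulers already issued, and need no new visit or sample.

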### **Adverse reaction**

An adverse reaction (AR) is any untoward or unintended response to an IMP. This means that a causal relationship between the IMP and an AE is at least a reasonable possibility, *i.e.*, the relationship cannot be ruled out. All cases judged by the reporting Investigator as having a reasonable suspected causal relationship to an IMP (*i.e.* possibly, probably or definitely related to an IMP) will qualify as AR.

### **Serious adverse events**

A SAE is an AE that results in any of the following outcomes, whether or not considered related to the study intervention:

- Death
- Life-threatening event (*i.e.*, the subject was, in the view of the Investigator, at immediate risk of death from the event that occurred). This does not include an AE that, if it occurred in a more severe form, might have caused death.
- Persistent or significant disability or incapacity (*i.e.*, substantial disruption of one's ability to carry out normal life functions)
- Hospitalization, regardless of length of stay, even if it is a precautionary measure for continued observation. Hospitalization (including inpatient or outpatient hospitalization for an elective procedure) for a pre-existing condition that has not worsened unexpectedly does not constitute a SAE.

- An important medical event (that may not cause death, be life-threatening, or require hospitalization) that may, based upon appropriate medical judgment, jeopardize the subject and/or require medical or surgical intervention to prevent one of the outcomes listed above. Examples of such medical events include allergic reaction requiring intensive care in an emergency room or clinic, blood dyscrasias, or convulsions that do not result in inpatient hospitalization.
- Congenital anomaly or birth defect

### **Serious adverse reaction (SAR)**

An AE (expected or unexpected) that is both serious and, in the opinion of the reporting investigator or Sponsors, believed to be possibly, probably or definitely due to an IMP or any other study treatments, based on the information provided.

### **Suspected unexpected serious adverse reaction (SUSAR)**

A SUSAR is a SAE that is unexpected and thought to be possibly, probably or definitely related to an IMP. No category of SAE has been defined as 'expected.'

### **Causality assessment**

For every unsolicited AE, an assessment of the relationship of the event to the administration of the vaccine will be undertaken. An intervention-related AE refers to an AE for which there is a probable or definite relationship to administration of a vaccine. An interpretation of the causal relationship of the intervention to the AE in question will be made, based on the type of event; the relationship of the event to the time of vaccine administration; and the known biology of the vaccine therapy.

Table 1: Guidelines for assessing the relationship of vaccine administration to an AE.

| Causality grading |                        | Explanation                                                                                                                                                                                                                                   |
|-------------------|------------------------|-----------------------------------------------------------------------------------------------------------------------------------------------------------------------------------------------------------------------------------------------|
| 0                 | No Relationship | No temporal relationship to study product and
Alternate etiology (clinical state, environmental or other interventions); and
Does not follow known pattern of response to study product                                   |
| 1                 | Unlikely        | Unlikely temporal relationship to study product and
Alternate etiology likely (clinical state, environmental or other interventions) and
Does not follow known typical or plausible pattern of response to study product. |
| 2                 | Possible        | Reasonable temporal relationship to study product; or
Event not readily produced by clinical state, environmental or other interventions; or
Similar pattern of response to that seen with other vaccines                 |
| 3                 | Probable        | Reasonable temporal relationship to study product; and
Event not readily produced by clinical state, environment, or other interventions or
Known pattern of response seen with other vaccines                            |
| 4                 | Definite        | Reasonable temporal relationship to study product; and
Event not readily produced by clinical state, environment, or other interventions; and
Known pattern of response seen with other vaccines                          |

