### **Study Termination Criteria**

The PI, sponsor's representative, the DSMB, and the appropriate regulatory authorities (national or international) may stop or suspend the use of this product at any time.

Significant numbers of arthritis cases have occurred among participant receiving the same vaccine, same batch number at high concentration from 1. 10^7 in Switzerland..

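### Annex causality Table 1 switches its reference from the study product (grades 0–1) to other vaccines (grades 2–4), so an unsolicited event typical only of this vaccine is graded too low or fits no row

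*Protocol*

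**What the plan says.** The annex section on causality assessment sets its scope as "For every unsolicited AE, an assessment of the relationship of the event to the administration of the vaccine will be undertaken". It lists three bases for the judgement: the type of event, its timing, and "the known biology of the vaccine therapy". It then defines which grades count: "An intervention-related AE refers to an AE for which there is a probable or definite relationship to administration of a vaccine".

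Table 1 below it has five grades, and each has a criterion on the pattern of the event:

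- Grade 0, No Relationship: "Does not follow known pattern of response to study product".
- Grade 1, Unlikely: "Does not follow known typical or plausible pattern of response to study product".
- Grade 2, Possible: "Similar pattern of response to that seen with other vaccines".
- Grades 3 and 4, Probable and Definite: "Known pattern of response seen with other vaccines".

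The protocol already records a signal tied to this product. Section 4.6, Study Termination Criteria, states: "Significant numbers of arthritis cases have occurred among participant receiving the same vaccine", and adds that it was the same batch at high concentration. Section 6.5 has vesicular lesions and tapped joint effusions sampled for virus.

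Section 6.5, Relationship to Investigational Product, holds a second five-level causality scale. It rests on clinical judgement, a plausible mechanism, timing and alternative causes, and does not mention other vaccines.

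**The concern.** One ordinal scale uses two reference standards. The lower two grades test the event against this product; the upper three test it against vaccines in general. An event that is characteristic of this live vector, but not of other vaccines, is therefore barred from the unrelated grades and earns no pattern credit in the related ones. That runs against the lead-in's own principle.

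The assessed relationship of unsolicited events to day 28 is part of a primary endpoint (section 4.3). The annex also draws its intervention-related line between Possible and Probable, so the step at which pattern credit is withheld can decide on which side of that line an event falls. In a first evaluation of a new vector, events peculiar to the product are the ones whose attribution matters most.

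**Working it through.** There is no plan figure to reproduce, because this is a check of the table's logic. Call the four facts about an event T (timing reasonable), N (not readily produced by another cause), S (fits the study product's known pattern) and O (fits a pattern of other vaccines). As written, the rows require:

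- Grade 0: no temporal relationship, and another cause, and not S.
- Grade 1: unlikely timing, and another cause likely, and not S.
- Grade 2: T or N or O.
- Grade 3: T and N or O. The operators can be read as T and (N or O), reading 1, or as (T and N) or O, reading 2.
- Grade 4: T and N and O.

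Cross three timings (reasonable, unlikely, none) with another cause likely or not, which gives six combinations. Take the highest grade met. Compare a product-only event (S true, O false) with a generic vaccine reaction (O true). Unlikely and no timing give the same result and share a line, so each of the last two lines stands for two combinations.

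| Timing | Other cause likely | Product-only event, both readings | Generic, reading 1 | Generic, reading 2 |
|---|---|---|---|---|
| Reasonable | No | 3 | 4 | 4 |
| Reasonable | Yes | 2 | 3 | 3 |
| Unlikely or none | No | 2 | 2 | 3 |
| Unlikely or none | Yes | no row | 2 | 3 |

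Results:

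- Under reading 1 the product-only event is lower or ungraded in 1 + 1 + 2 = 4 of 6 combinations and equal in 2. Under reading 2 it is lower or ungraded in 6 of 6. It is never higher.
- Grade 4 requires O, so a product-only event cannot reach Definite under either reading.
- With reasonable timing and another likely cause, the drop from 3 to 2 takes the event out of the intervention-related category under both readings. Under reading 1 this is the only combination in which a product-only event leaves that category. Under reading 2 the four poor-timing combinations do so as well, but that reading would let an event without reasonable timing be Probable on pattern alone.
- With poor timing and another likely cause, S excludes grades 0 and 1, and none of T, N or O holds for grade 2. No row fits.

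If the pattern criterion in grades 2–4 becomes (S or O), the product-only event takes the generic column's grade in all six combinations under both readings, and the empty cells disappear.

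Scope check. Section 6.5 lists joint ache, joint swelling or pain on motion, rash or blisters and mouth lesions as solicited, collected to day 14. Unsolicited events run to day 28. In section 4.3 the solicited endpoints are frequency and severity only; relationship appears only for unsolicited events. The table therefore bites directly on, for example, arthritis with onset after day 14. However, section 6.5 and the annex section on reporting procedures both ask for a causality assessment of every event, so the boundary is not sharp.

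**The case against.** The case against giving this much weight is substantial, and most of it limits the point rather than removing it.

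- The events that come to mind first, joint symptoms and blisters, are mostly solicited and so outside the table's stated scope. This stands, and it narrows the effect to later onset and to unsolicited terms.
- The annex defines an adverse reaction, a serious adverse reaction and a SUSAR from Possible upward, and the holding rule in section 4.6 does the same. A drop from Probable to Possible therefore removes nothing from these. This stands. Only an event that fits no row would leave their status undefined.
- The intervention-related definition appears once, and neither the endpoints nor section 7 applies a cut at Probable. This also stands.
- The table is headed as guidelines and the lead-in calls for interpretation, so an investigator could override the literal wording. That is true, but the annex also requires a second assessor, and two people overriding the same text need not agree.
- Section 5.7 mentions a related VSV vaccine given to 80 volunteers, so other vaccines could be taken to include this vector, and the annex grades arthralgia alongside headache and myalgia. The premise that arthritis is not a pattern of other vaccines is indeed an assumption. The change of reference between rows is there regardless.

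A reader might infer that a countable number of joint events will be lost among the 102 participants planned at 2×10^7 pfu (62 + 20 + 20). The documents do not support that. They give neither a joint-event rate nor the share with another likely cause, and most such events within 14 days would be solicited.

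**Conclusion.** The table is wrong as written, in a limited way. Its grades use two reference standards, contrary to its own lead-in. An unsolicited event that fits only this product's pattern cannot be Definite; it is Possible rather than Probable when timing is reasonable and another cause is likely; and it fits no row when timing is poor and another cause is likely.

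The effect falls mainly on the assessed relationship of unsolicited events, and no number of affected events can be given. The arthritis example assumes onset after day 14 and that arthritis is not a pattern of other vaccines.

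A reader might infer that product-specific harms will generally go unattributed or will escape the safety triggers. That goes too far. A well-timed event is still at least Possible, which is where those triggers start, and the no-row outcome is a corner case. Section 6.5 does not cure the defect, because the protocol does not say which of its two scales governs.

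**What to change.** In the Possible, Probable and Definite rows of annex Table 1, replace the reference to other vaccines by: *known for the study product (including its vector) or seen with other vaccines*. All five rows then recognise the study product's own pattern.

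Reconcile this table with the scale in section 6.5 and state that one scale applies, and to which events. Changing the three phrases alone would leave two competing scales.

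Check the unsolicited events already recorded against the corrected wording. At Amendment 3, 60 adults had been vaccinated, 59 of them in cohorts 1 and 2 (20 + 39) and one in cohort 3. The check is therefore short and will say little about the high dose; the gain is mostly in the grading still to come.

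The cost is three phrases, a cross-reference and a brief desk review. The small downside is that a few more events may be graded Probable or Definite.
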